## 6. METHODS

### MEASUREMENTS AND OUTCOME MEASURES

Given informed consent, data will be collected from the YHC-files of the participating families/children; parent-questionnaires to be completed at home; registration forms to be completed by YHC-professionals at the end of distinct YHC-contact moments (mainly process information); brief assessment forms to be completed by parents after distinct YHC-contact moments (process information). Anthropometrical measures (length, weight; waist circumference from age 24 months on) will be recorded according to standardized YHC protocols at the YHC-centers.

#### T0. DATA COLLECTION AT BASELINE (CHILD AGE CIRCA 1 MONTH)

The following data will be collected at baseline (T0).

- Pregnancy and delivery data: gestation; complications during pregnancy; mode of delivery; weight gain during pregnancy;
- Newborn: gender; birth ranking; birth weight and length; lowest weight; breast/bottle feeding;
- Parents: age; self-reported length and weight; health status; occupation; educational level; country of birth/ethnicity; history of weight problems; history of eating disorders;
- Siblings: gender; birth ranking; age; length and weight from file or parent-report.

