The 'Healthy toddler' intervention consists of an E-health module with tailored advice to parents regarding the 'BOFT' behaviors of their toddler and related child rearing practices, which is combined with face-to-face counseling in the setting of regular YHC at the child age of circa 18 months for the first time and at child age of circa 24 months for the second time. The E-health module is offered prior to both visits, and is repeated, as a reminder, a month after both visits. The face-to-face counseling will address specific issues raised by the E-health module, including questions that the parents may have. As proposed by the YHC-Overweight-prevention-protocol YHC-professionals will make use of motivational interviewing techniques in the two counseling sessions. As specific YHC-visiting schemes vary by region in the Netherlands, some variation will be allowed regarding age of application.

The study is designed as a cluster-randomized trial (c-RCT) with two intervention conditions (see above) and a control condition ('usual care'), with inclusion shortly after child birth, repeated measurements prior to and during the interventions, and a follow-up measurement at age 36 months, which is circa 12 months after the last intervention contact with the parents around the age of 24 months old in both intervention groups. The YHC-team (Consultatiebureau-team) is the unit of randomization in order to avoid contamination between the intervention condition and the control group condition within teams (Campbell et al., 2004).

Circa ten regional services providing Youth Health Care for preschool children (in Dutch: Jeugdgezondheidszorg 0-4 jaar, or Ouder- en Kindzorg) from metropolitan and non-metropolitan areas, to be selected in an open procedure, will participate in the study with a total of 45 Youth Health Care teams (Consultatiebureau-teams). Within each service, YHC-teams will randomly be assigned to either one of the two intervention groups or the control group. The last follow-up measurement in the study that we propose now will take place at the age of circa 36 months, during a regular visit to the YHC center in combination with a self-report questionnaire. A process and cost-effectiveness evaluation will accompany the effect evaluation. When the study is successful, follow-up projects with continuation of the interventions and/or follow-up measurements at older age will be proposed at ZonMw or other funding organizations in the future.

Figure 1.

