**TIME SCHEDULE IN MONTHS**

The schedule below is provided in months from the start of the project, which is scheduled at July 1, 2008.

0-6: Recruiting 45 YHC-centers, preparing procedures/measures/protocols, and (start of) training of YHC-professionals regarding 'BOFT+' (15 YHC-teams) and the 'Healthy toddler' (15 YHC-teams) interventions.

6-18: During a year 3.000 parents of newborns will be provided information about the study and will be asked informed consent by 60 YHC-teams (expected participation rate at least 50%).

6-19: After recruitment of 1.500 parents/newborns, baseline measurements (T0 at child age 1 month) will be performed in the 3 study arms.

6-19: In the 'BOFT+' study arm (15 YHC-teams) the 'BOFT+' intervention will be started regarding 500 parents/newborns at child age 1 month.

12-24: Measurements at child age 6 months in 1.500 parents/infants (T1).

21-33: Measurements at child age of 15 months in 1.500 parents/infants (T2).

23-37: In the 'Healthy toddler' study arm (15 YHC-teams) the first part of the 'Healthy toddler' intervention will be applied to 500 parents/toddlers at child age of circa 18 months.

29-43: In the 'Healthy toddler' study arm (15 YHC-teams) the second part of the 'Healthy toddler' intervention will be applied to 500 parents/toddlers at child age of circa 24 months.

30-42: In the 'BOFT+' study arm (15 YHC-teams) the last scheduled contact moment between YHC-team and parents regarding the 'BOFT+' interventions will take place regarding 500 parents/toddlers at child age 24 months.

42-54: Measurements at child age of 36 months in 1.500 parents/infants (T3).

6-55: Data entry, and data cleaning.

18-60: Analyses, dissemination of the results.

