#### T1. DATA COLLECTION AT CHILD AGE 6 MONTHS

The following data will be collected at child age 6 months (T1).

- Weight and length of the child (from YHC-file);
- History of breast/bottle feeding; supplemental feeding/introduction of solid food; family eating practices;
- Health and well-being of the parent: SF-12 (Gandek et al., 1998);
- In case of siblings in the family: Parent Problem Checklist (PPC) (Dadds et al., 1991);
- Health and well-being of the child: subscales of the Infant Toddler Quality of Life questionnaire (ITQOL) (Raaijmakers et al., 2007).

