#### T2. DATA COLLECTION AT CHILD AGE 15 MONTHS

The following data will be collected at child age 15 months (T2).

- Weight and length of the child (from YHC-file at age 14 months);
- History of breast/bottle feeding; supplemental feeding/introduction of solid food;

- Energy balance-related behaviors ('BOFT' behaviors): exercise and outdoor playing, having an appropriate family breakfast daily, sugar sweetened drinks consumption, and TV viewing, measured by parental questionnaires (Raaijmakers et al., 2007);
- Attitudes, motivation and perceived control of parents regarding the four energy balance-related ('BOFT') behaviors (Raaijmakers et al., 2007);
- Child rearing questionnaire for parents; Opvoedingsvragenlijst Voor Ouders (OVO) (Dekovic et al., 1991);
- Parenting style (PS) (Arnold et al., 1993);
- Parenting practices and rules (PP) (Arredondo et al., 2006);
- Health and well-being of the child: brief-Infant-Toddler Social and Emotional Assessment (brief ITSEA) (Briggs-Gowan et al., 2004).

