**Co-variables:**

- \*\* Pregnancy characteristics of the child, birth weight and length, lowest weight.
- \*\* Parents' and siblings' height and weight using self report and medical files. Self-report of adult height and weight has proven to be sufficiently accurate for epidemiological research (McAdams et al., 2007).
- \*\* Parents' health and well-being (SF-12; Parent Problem Checklist).
- \*\* General demographics, including educational level and ethnicity of the parents.
- \*\* Non response measures, including general demographics and reasons for non-participation

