**Information about the study, informed consent, invitation to participate, baseline measurements**

All parents of the children in the study population will, circa 2 weeks after birth, during a regular home visit by the YHC-nurse be informed about the study and will be invited to participate; this can be discussed at and informed consent can be given at the first regular visit to the YHC-center at age of circa one month old. Parents receive information about the study; informed consent form; and a brief questionnaire with items on background data (see above; data gathering at T0).

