## 7. STATISTICAL ANALYSIS

### **Intervention effect:**

To assess the intervention effect, multilevel analyses will be applied to allow for dependency between the individual measurements within the randomized YHC-teams (Campbell et al., 2004). The multilevel approach is also appropriate for the analyses regarding longitudinal data in the study. Multilevel linear regression analyses will be conducted for the continuous outcome variables with group (intervention or control) as independent variable and baseline values and potential confounders as covariates. Multilevel logistic regression will be performed in case of dichotomous outcome variables.

Additionally, effect modification by gender, parental educational level, ethnicity, and parental overweight status will be conducted by introducing an interaction term into the regression analyses. If this interaction term reaches statistical significance, stratified analyses will be carried out.

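### For BOFT+ versus control, the listed co-variables SF-12 and Parent Problem Checklist, and the planned 15- and 24-month covariates, are measured after the intervention has started

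*Protocol*

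**What the plan says.** **Start of BOFT+.** The time schedule in section 3 of the protocol states that the BOFT+ "intervention will be started regarding 500 parents/newborns at child age 1 month". It also identifies T0, at child age 1 month, as the baseline measurement.

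**What T0 holds.** The parent line of the T0 list in section 6 reads "Parents: age; self-reported length and weight; health status; occupation; educational level; country of birth/ethnicity; history of weight problems; history of eating disorders". The procedure part of section 6 calls the T0 form "a brief questionnaire with items on background data (see above; data gathering at T0".

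**What comes later.** The T1 list (6 months) contains "Health and well-being of the parent: SF-12 (Gandek et al., 1998", and the Parent Problem Checklist for families that already have other children. The T2 list (15 months) is the first to contain "Attitudes, motivation and perceived control of parents regarding the four energy balance-related ('BOFT') behaviors", the child-rearing questionnaire (OVO), the parenting style scale (PS) and the parenting practices scale (PP). Weight, length and waist are recorded again at 24 months.

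**How these enter the analysis.** The co-variable list in section 6 includes "Parents' health and well-being (SF-12; Parent Problem Checklist". Section 7 adjusts the intervention effect for "baseline values and potential confounders as covariates". The power section in section 4 adds that measurements at 15 and 24 months will serve as covariates, and expects more power from this.

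**The concern.** A covariate in a randomised comparison is safe when the intervention cannot have changed it. The SF-12, the Parent Problem Checklist and every 15- or 24-month value fail that condition for BOFT+, because the intervention is already running when they are taken.

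They are also close to what BOFT+ aims to change. Section 3 says it should raise parents' self-esteem, and describes the parenting style it promotes partly by low conflict between parents. Section 5 has parents act as a team in setting rules, and its BOFT+ flowchart covers crying and sleep rhythm. Parental well-being, parental conflict, attitudes and parenting may therefore be results of BOFT+. Section 7 itself treats parenting styles and practices as mediators.

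If the model adjusts for such variables, its group coefficient is no longer the total effect of BOFT+. Randomisation of teams gives no protection, because the distortion comes from the adjustment. The protocol presents the 15- and 24-month covariates as a gain in power, so the risk is easily missed.

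**Working it through.** **Step 1. Timing.** Taking 1 month as the start of BOFT+, and assuming the T0 form is completed before the first BOFT+ contact:

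| Measure | Role in the protocol | First value (or value proposed as covariate) | Months after BOFT+ start |
|---|---|---|---|
| SF-12 (parent) | co-variable | 6 months | 6 − 1 = 5 |
| Parent Problem Checklist | co-variable | 6 months, only families with siblings | 5 |
| Parental attitudes | secondary outcome | 15 months | 15 − 1 = 14 |
| OVO, PS, PP | secondary outcome, mediator | 15 months | 14 |
| Four child behaviours | primary outcome | 15 months, proposed as covariate | 14 |
| Child weight and length | used for primary outcome (BMI) | 24 months, proposed as covariate | 24 − 1 = 23 |
| Parental height and weight, education, ethnicity | co-variables, effect modifiers | T0 | none |
| Parental health status | T0 item | T0 | none |

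The BOFT+ flowchart shows its first themed contacts at about 3 and 4 months. Counting from there instead of 1 month, every row marked as later than the start still comes after it. All six parental scales (SF-12, Parent Problem Checklist, attitudes, OVO, PS, PP) lack a value from before BOFT+.

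**Step 2. What adjustment does.** Let τ be the total effect of BOFT+ on an outcome, δ its effect on a later-measured covariate, and b the association of that covariate with the outcome within arms. In a linear model the adjusted group coefficient is

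τ(adjusted) = τ − b × δ.

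This equals τ only if δ = 0 or b = 0. For 36-month BMI adjusted for 24-month BMI, δ is whatever BOFT+ has achieved on BMI by 24 months. If that effect is simply maintained to 36 months (δ = τ), the model reports τ × (1 − b). If the covariate and the outcome share unmeasured causes, the remaining coefficient can be off in either direction.

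**Step 3. The protocol's yardstick.** The power section gives 0.44 BMI points with SD 1.3, which is 0.44 / 1.3 = 0.338 SD.
- Cluster size 1,050 / 45 = 23.33; design effect 1 + (23.33 − 1) × 0.10 = 3.233; effective number per arm 350 / 3.233 = 108.2.
- One-sided alpha 0.05: (1.645 + 0.842) × 1.3 × √(2 / 108.2) = 0.439, which reproduces 0.44.
- Two-sided alpha 0.05: (1.960 + 0.842) × 1.3 × √(2 / 108.2) = 0.495, or 0.381 SD.

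The protocol does not state sidedness. That is a separate matter; the figure serves here only as a scale.

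**Step 4. Illustration for the SF-12 (both inputs assumed).** Suppose BOFT+ shifts the SF-12 by 0.1 to 0.3 SD and its association with an outcome is 0.1 to 0.3 SD per SD.
- b × δ runs from 0.1 × 0.1 = 0.01 SD to 0.3 × 0.3 = 0.09 SD.
- Against 0.338 SD this is 3% to 27%.
- For TV time (SD 32 min/day) it is 0.3 to 2.9 min/day, beside a stated detectable 11 min/day.

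No figure in the documents supports any particular value in these ranges.

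**Step 5. What the missing T0 scores cost by themselves.** With 15 teams per arm, the standard error of an arm difference is √(2 × (0.10 + 0.90 / 23.33) / 15) = 0.136 SD. Assume a T0 score correlating 0.3 to 0.5 with the 36-month value. If it explains only within-team variance, the standard error is multiplied by 0.987 to 0.965, a gain of 1% to 4%. If it explains variance at both levels, the factor is √(1 − 0.3²) = 0.954 to √(1 − 0.5²) = 0.866, a gain of 5% to 13%. The loss here is in precision.

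**The case against.** **Covariate choice belongs to the SAP.** Section 7 does not name the SF-12, and the co-variable list gives neither a time point nor a model. A SAP that is not shown may choose only T0 values. This is fair, and it makes the harm conditional. But the protocol does name the SF-12 and the Parent Problem Checklist as co-variables, neither has a T0 value, and the power section commits to 15- and 24-month covariates. A SAP that follows the protocol would carry the problem over.

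**The later values may be meant as repeated outcomes.** Section 7 says the multilevel approach also suits the longitudinal data. Used as outcomes, the 15- and 24-month values would be harmless. The power section, however, calls them covariates.

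**The design promise is kept.** Section 3 speaks of "repeated measurements prior to and during the interventions". T0 precedes BOFT+, and the 15-month visit normally precedes the first Healthy toddler application at about 18 months, although section 5 allows that from 14 months. The sentence does not promise every scale before both interventions, so this is not a contradiction.

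**Stronger readings that a reader might infer.**
- *BOFT+ has no pre-intervention parent data at all.* The quoted T0 line rules this out. It holds parental height and weight, education, ethnicity and health status. The first three are listed as co-variables, and education, ethnicity and parental overweight status are tested as effect modifiers.
- *The missing baseline scores bias the comparison.* They do not. Chance imbalance between randomised teams is already in the standard error. Selective consent would be a different problem, about recruitment.

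**Conclusion.** The point holds as a matter of covariate timing in the BOFT+ versus control comparison. The SF-12 and the Parent Problem Checklist are listed for adjustment but first measured 5 months after BOFT+ starts. The planned 15- and 24-month covariates come 14 and 23 months after it. These variables lie on or near the intended pathway, so adjusting for them can remove or distort part of the effect. The T0 parent variables are unaffected, and the randomised comparison remains valid if it is unadjusted or adjusted for T0 values only.

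The size cannot be derived from the documents. The 0.01 to 0.09 SD for the SF-12 rests wholly on assumed inputs, and its lower end is negligible. Adjusting 36-month BMI for 24-month BMI could matter more, because the covariate is then an earlier value of the outcome itself, but the documents give no figure for that either. The conclusion assumes that T0 is completed before the first BOFT+ contact and that the co-variables are used as listed.

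**What to change.** **Analysis (no added data collection).** State in section 7, and align the co-variable list and the power section with it: *In the BOFT+ versus control comparison only variables measured at T0 are used as covariates. The SF-12, the Parent Problem Checklist and all values at 15 and 24 months are excluded as adjustment covariates and are analysed as outcomes or mediators.* The T0 health status item can then stand in as the parental health covariate. The power section should drop the expected gain from 15- and 24-month covariates for this comparison. That expected precision is given up, because it depends on adjusting for post-intervention values.

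**Data collection, if T0 can still be changed.** Specify the parental health status item at T0 as the SF-12, in all three arms. The cost is a slightly longer form for parents of newborns, which may slightly lower its return.

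**Optional.** Add attitude or OVO items at T0 only where a parent of a newborn can answer them. The documents do not show which items those are, and the gain is mainly in precision, so this is a trade-off and not a requirement.

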#### T1. DATA COLLECTION AT CHILD AGE 6 MONTHS

The following data will be collected at child age 6 months (T1).

- Weight and length of the child (from YHC-file);
- History of breast/bottle feeding; supplemental feeding/introduction of solid food; family eating practices;
- Health and well-being of the parent: SF-12 (Gandek et al., 1998);
- In case of siblings in the family: Parent Problem Checklist (PPC) (Dadds et al., 1991);
- Health and well-being of the child: subscales of the Infant Toddler Quality of Life questionnaire (ITQOL) (Raaijmakers et al., 2007).

#### T2. DATA COLLECTION AT CHILD AGE 15 MONTHS

The following data will be collected at child age 15 months (T2).

- Weight and length of the child (from YHC-file at age 14 months);
- History of breast/bottle feeding; supplemental feeding/introduction of solid food;

- Energy balance-related behaviors ('BOFT' behaviors): exercise and outdoor playing, having an appropriate family breakfast daily, sugar sweetened drinks consumption, and TV viewing, measured by parental questionnaires (Raaijmakers et al., 2007);
- Attitudes, motivation and perceived control of parents regarding the four energy balance-related ('BOFT') behaviors (Raaijmakers et al., 2007);
- Child rearing questionnaire for parents; Opvoedingsvragenlijst Voor Ouders (OVO) (Dekovic et al., 1991);
- Parenting style (PS) (Arnold et al., 1993);
- Parenting practices and rules (PP) (Arredondo et al., 2006);
- Health and well-being of the child: brief-Infant-Toddler Social and Emotional Assessment (brief ITSEA) (Briggs-Gowan et al., 2004).

### **TO BE REGISTERED IN YHC-CENTERS (24 MONTHS)**

Additionally will be recorded at child age 24 months:

Weight and length of the child, and waist circumference.

### **T3. DATA COLLECTION AT CHILD AGE 36 MONTHS**

The following data will be collected at child age 36 months (T3).

- Weight and length of the child, and additionally waist circumference (from YHC-file at age 36 months);
- Energy balance-related behaviors ('BOFT' behaviors): exercise and outdoor playing, having an appropriate family breakfast daily, sugar sweetened drinks consumption, and TV viewing, measured by parental questionnaires (Raaijmakers et al., 2007);
- Attitudes, motivation and perceived control of parents regarding the four energy balance-related ('BOFT') behaviors (Raaijmakers et al., 2007);
- Child rearing questionnaire for parents; Opvoedingsvragenlijst Voor Ouders (OVO) (Dekovic et al., 1991);
- Parenting style (PS) (Arnold et al., 1993);
- Parenting practices and rules (PP) (Arredondo et al., 2006);
- Parent Problem Checklist (PPC) (Dadds et al., 1991)
- Parents: self-reported length and weight;
- Siblings: length and weight from YHC-files (if available);
- Health and well-being of the parent: SF-12 (Gandek et al., 1998);
- Health and well-being of the child: subscales of the Infant Toddler Quality of Life questionnaire (ITQOL) (Raaijmakers et al., 2007);
- brief-Infant-Toddler Social and Emotional Assessment (brief ITSEA) (Briggs-Gowan et al., 2004).

**The primary outcome measures:**

- \*\* Energy balance-related behaviors: exercise and outdoor playing, having an appropriate family breakfast daily, sugar sweetened drinks consumption, and TV viewing, measured by parental questionnaires (Raat et al., 2007).
- \*\* BMI (weight/height) according to standardized procedures during scheduled YHC visits; waist circumference (Eisenmann et al., 2004).
- \*\* Additionally: Proportion of overweight children based on internationally accepted gender and age-specific cut-off values (Cole et al., 2000)
- .

**The secondary outcome measures:**

- \*\* Attitudes, motivation and perceived control of parents regarding the four energy balance-related ('BOFT') behaviors (Raat et al., 2007).
- \*\* General parenting styles and parental practices and rules. These will be measured by Child rearing questionnaire for parents (Opvoedingsvragenlijst Voor Ouders; OVO) (Dekovic et al, 1991); Parenting style (PS) (Arnold et al., 1993); Parenting practices and rules (PP) (Arredondo et al, 2006).
- \*\* Child's health and well-being: Infant Toddler Quality of Life questionnaire (ITQOL) (Raat et al., 2007); brief-Infant-Toddler Social and Emotional Assessment (ITSEA) (Briggs-Gowan et al., 2004).

**Co-variables:**

- \*\* Pregnancy characteristics of the child, birth weight and length, lowest weight.
- \*\* Parents' and siblings' height and weight using self report and medical files. Self-report of adult height and weight has proven to be sufficiently accurate for epidemiological research (McAdams et al., 2007).
- \*\* Parents' health and well-being (SF-12; Parent Problem Checklist).
- \*\* General demographics, including educational level and ethnicity of the parents.
- \*\* Non response measures, including general demographics and reasons for non-participation

